### Statistical methods

All data will be analyzed using the PASW Statistics 21 software (SPSS) (IBM, Armonk, NY, USA). During all study, two trained and calibrated examiners will evaluate the treated teeth clinically and radiographically. Inter- and intra-examiner reliability will be verified by casual and systematic error. The Kolmogorov-Smirnov test will be adopted to test the normality of continuous variables, which will be expressed as median for the variables with a non-normal distribution and a mean value ± SD for the variable with a normal distribution. The Wilcoxon signed rank test will compare the clinical and radiographic outcomes over period. The Mann-Whitney test will compare the clinical and radiographic outcomes between groups. Paired *t* test will be used to compare the radiographic measurements over time. Independent *t* test will compare the radiographic measurements between groups. The level of significance of 5% will be adopted for all comparisons. The logistic regression will be applied, and the degrees of this association will be measured using odds ratio (OR) and 95% confidence interval (95% CI).

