## Methods/design

### Study design

In primary teeth, vital pulp therapy goals are the pulp tissue regeneration and the maintenance of the physiological process of deciduous tooth exfoliation. Despite its biocompatibility, MTA has a longer setting time, difficult handling, high cost, and potential for tooth discoloration. Thus, this study aims to evaluate clinically and radiographically the pulp repair after the use of a new dentin-pulp biostimulation chitosan membrane in primary teeth with deep occlusal and occlusoproximal cavities reaching more than 3/4 of the total thickness of carious dentin evaluated by periapical radiograph, with at least two thirds of root length. This will be a double-blinded parallel-group randomized controlled trial composed of two groups: group 1 (G1—control), teeth treated with mineral trioxide aggregate (MTA), and group 2 (G2—experimental), teeth treated with the new dentin-pulp biostimulation chitosan membrane.

Before study group assignment, the allocation concealment will be performed to trial participants in sequentially numbered, sealed envelopes. This closed envelope will include a randomization number. Allocation concealment will be ensured, as the team responsible will not release the randomization number until the patient has been recruited into the trial. The operator will open the envelope and will find the treatment condition to be conducted in the patient. The operator then gives the information about treatment allocation to the patient. The team responsible for recruitment is not allowed to receive information about the group allocation.

One primary tooth per patient will be randomly allocated in each group. If the patient has more than one tooth to include in the study, the tooth closest to the inclusion criteria will be chosen. The allocation criteria will be the cavity type (occlusal and occlusoproximal) and the child’s age. Group allocation will be randomized through computerized stratified sampling (Microsoft Excel®), independently, that is, the patients and legal guardians will remain blinded to intervention group status. Randomization will occur close to the moment of the intervention [18]. Blinding the operator during the allocation sequence and application step will not be possible. The intervention group identifier will be assigned at random and will not be identified during data analysis, that is, the examiners will remain blinded.

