### Sample size

The minimum sample size calculation was performed based on data from a previous study that found clinical and radiographic success of 94.73% for teeth treated with MTA [14]. For the sample calculation, alpha and beta errors of 5% and 20% will be respectively considered. The sample size also provides 80% power. The sample will be of 143 teeth per group to detect significant differences. A dropout rate of 20% will be estimated, and then, the number of eligible teeth will be 234 per group.

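### Allocation is stratified by cavity type and age, but the named between-group tests use neither factor, and the logistic regression is not stated to include treatment or the strata

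*Protocol article*

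**What the plan says.** Under Study design, the protocol article states: "The allocation criteria will be the cavity type (occlusal and occlusoproximal") and the child's age. It adds: "Group allocation will be randomized through computerized stratified sampling". No block size or other balancing rule is given, and the age categories are not stated.

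Under Statistical methods, two between-group tests are named. For the clinical and radiographic criteria: "The Mann-Whitney test will compare the clinical and radiographic outcomes between groups". For the dentin barrier: "Independent *t* test will compare the radiographic measurements between groups". The abstract repeats both. A model is also planned: "The logistic regression will be applied, and the degrees of this association will be measured using odds ratio (OR) and 95% confidence interval (95% CI"). Its outcome, exposure and covariates are not named. On error rate: "The level of significance of 5% will be adopted for all comparisons".

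The Background frames the question as whether the membrane has a clinical and radiographic success rate comparable to that of MTA.

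**The concern.** Factors that are important enough to stratify on are normally carried into the analysis. Where strata predict outcome and the arms are balanced within them, the treatment difference varies less than an unstratified test assumes. That test then rejects too seldom and gives up part of the precision that stratifying bought. Where balance is not forced, the unstratified test keeps its error rate, but it still leaves explainable variation in the residual.

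A second point does not depend on the strata. Most of the clinical and radiographic criteria are present or absent. On such data Mann-Whitney is a tie-corrected comparison of two proportions. It returns a p-value but no difference in success, and a non-significant p-value does not show that two materials are comparable.

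**Working it through.** **Inputs from the protocol article.** MTA success 94.73%, 143 teeth per group, 234 per group after the dropout allowance, and 20% dropout (Sample size). The 5% level is taken as two-sided, since sidedness is not stated.

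**Inputs that must be assumed.** The article gives no success rates by stratum and no figure for how much of the variation in thickness the strata explain. Both are shown as ranges. The first two calculations assume balance forced within strata.

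The article has no figure of its own on this point to reproduce.

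**Success.** Take two equal strata with mean success 0.9473 and a gap g between them.
- Total variance = 0.9473 × 0.0527 = 0.04992.
- Within-stratum variance = 0.04992 − (g/2)².
- SE ratio r = √(total / within). True alpha of the unstratified test = 2(1 − Φ(1.96 r)).

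| Gap | Within variance | SE overstated | True alpha |
|---|---|---|---|
| 2 points | 0.04982 | 0.1% | 0.0498 |
| 6 points | 0.04902 | 0.9% | 0.0479 |
| 10 points | 0.04742 | 2.6% | 0.0443 |

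A simulation of 20,000 trials (two strata, 71 teeth per stratum per arm) agrees. Type I error of tie-corrected Mann-Whitney versus the Mantel-Haenszel test was 0.049 and 0.049 with no gap, 0.045 and 0.049 at 6 points, and 0.044 and 0.051 at 10 points.

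**Dentin barrier thickness.** If the strata explain a share R² of the variance, r = 1/√(1 − R²). Take an effect of 2.80 unadjusted standard errors, which gives a nominal 80% power (1.96 + 0.84). Then unadjusted power = Φ(0.84/√(1 − R²)) and adjusted power = Φ(2.80/√(1 − R²) − 1.96).

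| R² | SE overstated | True alpha | Power, unadjusted | Power, adjusted |
|---|---|---|---|---|
| 5% | 2.6% | 0.044 | 0.81 | 0.82 |
| 10% | 5.4% | 0.039 | 0.81 | 0.84 |
| 20% | 11.8% | 0.028 | 0.83 | 0.88 |
| 30% | 19.5% | 0.019 | 0.84 | 0.92 |

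At R² = 0 there is no overstatement. Without forced balance, the unadjusted test stays at 5% and about 80% power, and adjustment still gains precision. The 80% benchmark is borrowed, because the trial is sized on success and not on thickness.

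**What the missing estimate hides.** With 143 teeth per arm and both arms at 94.73%, the SE of the difference is √(2 × 0.04992/143) = 0.0264, so the 95% CI half-width is 1.96 × 0.0264 = 5.2 points. An observed difference of zero would therefore be compatible with failures roughly doubling from 5.27%. Only an interval shows this.

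**Failures available to a logistic model.** Analysable teeth are taken as 2 × 143 = 286, or 2 × 187 = 374 (234 × 0.80 = 187).
- Both arms at the MTA rate: 286 × 0.0527 = 15; 374 × 0.0527 = 20.
- BBio 10 points lower: 143 × (0.0527 + 0.1527) = 29; 187 × 0.2054 = 38.

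The article gives no BBio rate, so both cases are assumptions.

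**The case against.** Three counter-arguments carry weight.

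First, a reader might infer that the planned standard errors are simply too wide. The article does not support that. It requires strata that predict outcome and balance forced within them, and neither is shown. Under simple randomisation inside strata, the unadjusted standard error is not systematically too large. This stands, and the conclusion is conditional for that reason.

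Second, a reader might infer that no adjusted treatment effect will be produced. The logistic regression could contain treatment, cavity type and age and yield an adjusted odds ratio. A covariate list is something an article may leave to an analysis plan, so its absence alone is no fault. This also stands. What remains is that the article positively names unstratified tests as the group comparisons, and an analysis plan that adjusted would have to replace them. An odds ratio is also not a difference in success.

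Third, the larger figures (true alpha of 0.028 or 0.019) belong to a continuous measure under assumed R² of 20% and 30%. They must not be read as applying to success, where the effect is slight. In either case the error is conservative and creates no false positives.

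It can fairly be added that the lack of a risk difference is a reporting issue that would exist without stratification. That is true, but the same change of analysis resolves both.

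**Conclusion.** The point holds in a limited form. The design stratifies on two factors, the named between-group tests use neither, and the one model that could use them is not stated to do so. Validity is not threatened, because type I error stays at or below 5%. For success, the loss from ignoring the strata is negligible to small. For thickness it ranges from nothing to material, depending on an R² that the article does not supply. The gap that needs no assumption about the strata is that Mann-Whitney gives no difference in success with a confidence interval, although the stated question is comparability with MTA. The change is worth making, but it is not a critical defect.

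**What to change.** - **Success at 12 and 24 months.** Make the between-group analysis a Mantel-Haenszel risk difference with 95% CI, stratified by cavity type and by the age groups used for allocation, in place of Mann-Whitney.
- **Logistic regression.** State that the model contains treatment, cavity type and age. Use a penalised (Firth) fit if failures are few.
- **Radiographic measurements.** Replace the independent t test with a linear model of the measurement on treatment, cavity type and age, reporting the adjusted mean difference with 95% CI.

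Both factors are already needed for allocation, so no new data are collected. The cost is revised wording, settled before outcomes are compared by group, and slightly more analysis work. The software named in the plan should be checked for the stratified risk difference and the penalised fit.

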Control group—MTA (Angelus®, Londrina, Paraná, Brazil) will be mixed on sterile glass plate according to the manufacturer’s instruction (1 powder spoon to 1 drop of distilled water) for 30 s and placed onto the pulp stumps with the aid of spatula and sterile cotton pellet moistened with distilled water. A thin layer of the material will be assured, based on previous studies [14, 30, 31, 33, 34].BBio group—the dentin-pulp biostimulation chitosan membranes will be previously prepared in the laboratory with equal parts containing 1.5 g of chitosan (Sigma Aldrich, St. Louis, USA), 1.5 g of alginate, and 1.5 g portland cement-based. Each layer will be individually placed and dried at 30 °C for 15 min. Then, the membrane (composed of three layers) will be dried for more 24 h [25, 26]. After preparation and sterilization, the membrane will be placed on the pulp stumps.

For both groups, a thin layer of liner material (Cimpat white – Septodont, Pomerode, Santa Catarina, Brazil) will be placed onto the study materials, inside the pulp chamber. The final restorations will be performed with resin-modified glass ionomer cement (Vitremer® 3M/ESPE) [28–31]. Just after vital pulp therapy, a periapical radiograph will be taken (immediate postoperative radiograph) [28–30]. The follow-up periods will be 12 and 24 months after treatment [31, 35] (Fig. 1).

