#### Measurement of the dentin barrier

After the scanning of the radiographs, the images will be analyzed in Image J2 software version 64 bits (National Institutes of Health, NY, USA) [37]. The measurements on the digitized radiographs will be performed at the immediate postoperative period and 12 and 24 months of follow-up. All measurements of the scanned images will be performed by a trained and calibrated examiner blinded to the clinical procedure and the pulp capping materials to perform the measurement of dentin barrier thickness, and points will be marked on the center of the capping material layer (point A) and on the center of the furcal area (point B) [37]. Intra-examiner calibration will be determined by the casual and systematic error [36]. To assure reproducibility, each image will be measured twice at 15-day interval. The mean of these two measurements will be used for the comparisons.

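### The between-group test of the dentin barrier makes no stated use of the immediate postoperative distance, so any difference in capping-layer thickness and stable tooth anatomy stay in the comparison

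*Protocol article*

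**What the plan says.** The protocol article defines the distance under Measurement of the dentin barrier: "points will be marked on the center of the capping material layer (point A) and on the center of the furcal area (point B". On timing it says: "The measurements on the digitized radiographs will be performed at the immediate postoperative period and 12 and 24 months of follow-up". Each image is read twice, 15 days apart, and "The mean of these two measurements will be used for the comparisons".

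Statistical methods then gives two tests for this outcome. Within groups: "Paired *t* test will be used to compare the radiographic measurements over time". Between groups: "Independent *t* test will compare the radiographic measurements between groups". The abstract repeats this split. Neither place names a between-group analysis of change or an adjustment for the immediate postoperative distance.

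Clinical procedures describes two physically different layers. MTA is mixed and placed by hand: "A thin layer of the material will be assured, based on previous studies". The BBio material is made beforehand in the laboratory: "Then, the membrane (composed of three layers) will be dried for more 24 h". No thickness is given for either.

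**The concern.** Two things enter the measured distance that are not new dentin.

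- **Capping layer.** Point A lies at the centre of the layer, so about half its thickness lies inside the distance. A paste placed by hand and a preformed three-layer membrane need not be equally thick. Randomisation cannot balance a difference that the treatment itself creates, and blinding the examiner does not remove it.
- **Tooth anatomy.** Eligibility admits upper and lower, first and second primary molars in children aged 5 to 9. Randomisation balances anatomy in expectation, so it does not bias the comparison, but it adds to the error term.

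The immediate postoperative film records both for each tooth before any barrier has formed. Used only in paired tests within each arm, it cannot help the comparison of materials: a significant change in one arm and not in the other is not a test of BBio against MTA. At stake is whether a group difference in this outcome can be attributed to dentin.

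**Working it through.** The protocol states no SD, effect size, correlation or power for the barrier distance, so there is no figure of its own to reproduce.

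**1. What the landmarks imply.** Let D be the measured distance, T the layer thickness, and d the part from the pulpal border of the layer to point B. With A at mid-thickness, D = d + T/2. If mean thickness differs between materials by dT, the raw group difference is

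(difference in d) + dT/2.

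**2. How much this could matter.** Inputs: n = 143 per group (Sample size, before dropout); 5% significance level (Statistical methods; two-sided assumed); dT in units of the SD of the raw distance (assumed). With no true difference, and a standard error of √(2/143) = 0.118 SD, the normal-approximation rejection probability is

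Φ(b/0.118 − 1.96) + Φ(−b/0.118 − 1.96), with b = dT/2.

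| Assumed dT (SD) | Shift b (SD) | Probability of a significant result |
|---|---|---|
| 0.10 | 0.05 | 0.071 |
| 0.25 | 0.125 | 0.185 |
| 0.50 | 0.25 | 0.561 |
| 0.75 | 0.375 | 0.887 |
| 1.00 | 0.50 | 0.988 |

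The nominal value is 0.05.

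**3. Change from the immediate film.** Subtracting gives D(t) − D(0) = [d(t) − d(0)] + [T(t) − T(0)]/2. If the layer keeps its thickness, the second bracket is zero and the offset cancels. If one material thins more than the other, half the difference in thinning remains.

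**4. Precision.** Assume equal variances at the two times and correlation r. Relative to the raw variance, change has 2(1 − r). The difference detectable with 80% power at n = 143 per group is (1.96 + 0.84) × 0.118 = 0.33 SD for the raw comparison, and is multiplied by √[2(1 − r)] for change.

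| Assumed r | Variance of change / raw | Detectable difference, change (SD) |
|---|---|---|
| 0.3 | 1.40 | 0.39 |
| 0.5 | 1.00 | 0.33 |
| 0.7 | 0.60 | 0.26 |
| 0.9 | 0.20 | 0.15 |

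**5. ANCOVA with the centre landmark.** Its variance factor, 1 − r², is smaller (0.91, 0.75, 0.51 and 0.19 at the same r). But the immediate distance is itself shifted by dT/2 in one arm. Under equal variances the slope is r, so the adjusted difference keeps dT/2 − r × dT/2 = (1 − r) × dT/2. At r = 0.7 that is 0.15 dT, and at r = 0.9 it is 0.05 dT. ANCOVA removes the offset only in part.

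**The case against.** The strongest reply is that the article does not say whether the compared measurements are raw distances or changes, and that such a choice may sit in an analysis plan that is not shown. Averaging two readings is a reproducibility step, and the average could feed a change score. This is fair as far as it goes. But the only value defined for the comparisons is a mean per image, no change is defined anywhere, and the abstract gives the same paired and independent split. If change was intended, one sentence settles it.

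Other replies stand at least in part:

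- A reader might infer that the barrier result will be an artefact of layer thickness. The documents do not support that. No thickness is given, the MTA layer is described as thin, and the two layers could turn out alike.
- A reader might infer that the immediate postoperative value is ignored. It is not: it enters the paired tests, and an independent t test on the immediate film would reveal a starting offset. That test would not correct the 12- and 24-month comparisons.
- The centre of the layer could mean its mesiodistal midpoint, with depth left open. Mid-thickness is the natural reading, but not the only one.
- Change is not always more precise, since no correlation is documented.
- The Discussion says the method was chosen because the exact barrier thickness is hard to evaluate and roots overlap. Moving point A is therefore not free of risk.
- The stated hypothesis and the sample size concern clinical and radiographic success, which limits the consequence to this outcome.

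**Conclusion.** The point holds in a limited form. The one stated comparison of materials on the dentin barrier is an independent t test with no stated use of each tooth's immediate postoperative distance, although that distance is planned for every tooth. If the test is run on raw distances with A at mid-thickness, it is shifted by half of any thickness difference. With 143 per group the false-positive rate is about 7% at dT = 0.1 SD, 56% at 0.5 SD and 99% at 1.0 SD. These rates rest wholly on assumed values of dT, and the true size and direction are unknown. The claim is that the planned test cannot separate layer thickness from dentin, not that such a difference exists. The gain in precision from using change is likewise conditional: it appears only if r exceeds 0.5.

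**What to change.** State that the between-group comparison is made on change from the immediate postoperative film (12 months minus immediate, and 24 months minus immediate). Use a linear model with treatment and the two stratification factors, cavity type and age. Report the within-group paired t tests as descriptive.

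The cost is a few lines of analysis wording; no film, visit or patient is added. There are two downsides: precision is lost if r is below 0.5, and the offset cancels only while the layer keeps its thickness. ANCOVA on the immediate distance should not replace change while A stays at the centre of the layer, because that covariate is affected by treatment.

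Marking A at the pulpal border of the layer would take thickness out of the distance directly. Treat this as optional, to be adopted before measurement begins and only if examiner calibration shows that the border can be read reliably, given the difficulty stated in the Discussion. In either case, say in one sentence where in the depth of the layer point A lies.

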### Outcomes

#### Clinical and radiographic evaluations

The teeth will be clinically and radiographically evaluated at 12 and 24 months regarding the pulp response [28–30]. During the follow-up assessment, the following clinical criteria will be verified: spontaneous pain; any signs of mobility, sensitivity to percussion, abscess/fistula, gingival swelling not caused by poor oral hygiene, and restoration failure. The radiographic criteria will include presence/absence of internal/external resorption, signs of furcal impairment, advanced rhizolysis stage, and restoration failure including fracture and loss. Two previously trained and calibrated blinded examiners will perform the clinical and radiographic assessments. Examiners will be previously trained and calibrated in relation to the clinical and radiographic criteria in a pilot study, based on previous studies [30, 31, 33]. Inter- and intra-examiner reliability will be verified by casual and systematic error [36]. The examiners will fill in a form with all data for further analyses of the results.

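### All comparisons are tested at 5% and neither an outcome nor a visit is named primary, so the error rate for the success hypothesis exceeds 5%: about 8–10% or 13–18.5%, depending on how success is read

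*Protocol article*

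**What the plan says.** The Statistical methods section of the protocol article sets one rule for all tests: "The level of significance of 5% will be adopted for all comparisons". The between-group tests it lists are a Mann-Whitney test for the clinical and the radiographic outcomes and an independent t test for the radiographic measurements. Within-group tests over time and a logistic regression, whose outcome and visit are not given, come on top.

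Under Outcomes, two visits have equal standing: "The teeth will be clinically and radiographically evaluated at 12 and 24 months regarding the pulp response". The barrier measurement is taken at the same two visits and immediately after the operation.

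The null hypothesis, at the end of the Background, is that the membrane and MTA have comparable success, judged clinically and on radiographs. The Sample size section starts from one rate, "clinical and radiographic success of 94.73% for teeth treated with MTA", with "alpha and beta errors of 5% and 20% will be respectively considered", and adds: "The sample size also provides 80% power". Neither place says whether success is one combined outcome or two, or at which visit it is judged.

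**The concern.** The sample size rests on one success rate, but the analysis offers several tests that could each be taken as the answer, all at 5% and none ranked first. If the materials are truly equal, each further look at success adds a chance of a spurious difference, and with it a rejection of the trial's own hypothesis. With no lead comparison fixed, the one to be stressed can be chosen after the results are known. The power statement is affected as well: 80% power describes one test, and the article does not say which.

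**Working it through.** **The plan's own figure.** The 143 teeth per group cannot be derived from the stated inputs, because no success rate or difference is given for the membrane group. With an assumed 10-point difference (94.73% against 84.73%, mean 89.73%), two-sided 5%, 80% power and no continuity correction:

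n = [1.96 × √(2 × 0.8973 × 0.1027) + 0.842 × √(0.9473 × 0.0527 + 0.8473 × 0.1527)]² / 0.10² ≈ 143.5, so 144 when rounded up.

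The stated size therefore fits a single comparison of two proportions at 5%, with no allowance for further tests. The difference is an assumption; the point does not depend on it.

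**Counting the between-group tests** (Statistical methods and Outcomes):

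- Success as one combined outcome, at 12 and 24 months: 2 tests.
- Clinical and radiographic outcomes separately, at 12 and 24 months: 4 tests.
- The same four plus barrier thickness at 12 and 24 months: 6 tests.

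Within-group tests are left out because they do not compare the materials. The logistic regression is left out because its outcome and visit are not named.

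**Chance of at least one false significant result when the materials are equal.** For k independent tests at 5% it is 1 − 0.95^k:

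- k = 2: 1 − 0.9025 = 9.75%
- k = 4: 1 − 0.8145 = 18.5%
- k = 6: 1 − 0.7351 = 26.5%

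The tests are not independent, since the same teeth are seen at both visits. The other columns come from simulated normal test statistics with a common assumed correlation, each tested two-sided at 5%:

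| Tests | Corr. 0 | 0.5 | 0.7 | 0.8 | 0.9 |
|---|---|---|---|---|---|
| 2 (combined success) | 9.75% | 9.1% | 8.4% | 7.9% | 7.0% |
| 4 (clinical, radiographic) | 18.5% | 15.5% | 13.0% | 11.4% | 9.4% |
| 6 (with barrier) | 26.5% | 20.7% | 16.4% | 13.8% | 10.8% |

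With correlations that differ by pair (0.7 between visits, 0.5 between clinical and radiographic outcomes, 0.1 with barrier thickness), four tests give about 15% and six about 22%. All these correlations are assumptions; the article gives none.

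**Discreteness.** A Mann-Whitney test on a yes/no outcome with 94.73% success and 143 teeth per group has an actual size of about 4.8%, so using 5% per test changes little.

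**The case against.** The strongest reply is that this is mostly silence. The quoted sentence gives a nominal level and does not say that all tests are confirmatory. A journal article may leave the ranking of outcomes to a full protocol or analysis plan that is not shown. The hypothesis and the sample size also point to success as the lead quantity.

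Part of this stands. Success is recognisably the lead quantity, so what is open is narrower: one outcome or two, and which visit. But the article does not merely omit a ranking. It states a flat level for every comparison, and a plan that ranked or adjusted the tests would have to depart from that sentence.

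Three stronger readings are tempting, and the document does not support them.

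- A reader might take 16–26.5% as the error rate for the trial's hypothesis. That range counts two barrier-thickness tests, and a difference in thickness cannot reject a hypothesis about success rates. Its upper end also needs independent tests. That is unrealistic: visits share teeth, and restoration failure is in both the clinical and the radiographic list.
- A reader might count each clinical and radiographic criterion as a separate test and reach much higher figures. The Statistical methods section plans no test by criterion.
- A reader might add that the authors could call the materials comparable after a non-significant result. That is a separate question, about reading non-significance as equivalence, and naming a primary comparison would not cure it.

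**Conclusion.** The point holds in a limited form. Following the article as written, success can be tested at two visits, as one outcome or two, each time at 5%. For equal materials the chance of at least one false difference in success is about 8–10% on the combined reading and about 13–18.5% on the two-outcome reading, against a nominal 5%. Counting the barrier tests gives about 16–26.5% for any false between-group difference.

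These ranges rest on the test counts above and on assumed correlations from 0.7 down to 0. At correlations of 0.8 or 0.9 the figures are lower, but every case in the table stays above 5%. The stated power cannot be attached to a particular test until the outcome and visit are named. This should be corrected; it does not invalidate the design.

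**What to change.** In Statistical methods, replace the sentence on the significance level. Name combined clinical and radiographic success at one visit as the single primary comparison, tested at 5%, and fix this before any between-group data are seen. The final visit at 24 months is one reasonable choice, but the document favours neither visit, so the authors must decide. State in Sample size that the power refers to this comparison. Declare all other comparisons secondary: the other visit, the separate clinical and radiographic results, barrier thickness, the within-group tests, and any logistic regression that is not the primary analysis. Report them as estimates with 95% confidence intervals and make no confirmatory claim.

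The false-positive chance for the primary claim is then 5%. The cost is a few lines of text and no extra teeth; the downside is that secondary results can no longer be presented as confirmatory. The alternative, a Bonferroni correction over six tests (0.05/6 = 0.0083 each), keeps the overall rate at or below 5%. Under the assumed 10-point difference, however, it raises the requirement from 144 to 222 teeth per group before dropout, so naming one primary comparison is much cheaper.
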